### Outcomes measures

2.7

#### Primary outcome

2.7.1

1.Resistin, serum amyloid P component, C-reactive protein, and D-dimer are the candidate indicators that seem effective in diagnosing blood stasis based on previous studies on blood stasis.^[12–15]^2.Blood stasis score: A blood stasis questionnaire used to assess the presence/absence of blood stasis and to evaluate the blood stasis score was developed by the Korea Institute of Oriental Medicine through a blood stasis diagnosis technique development research project.^[16–18]^ It was executed for 5 years from 2013 to 2018, and it showed high reliability and validity.^[17,18]^ We extracted 31 questions related to metabolic disorders from the blood stasis questionnaire using the experts’ delphi method and validity analysis, in order to use it as an assessment tool in this study.^[19]^ By referring to the standard operating procedure of each question, a Korean medicine doctor will directly interview each patient and complete the blood stasis questionnaire (Supplemental Digital Content (Appendix 1)).

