#### Inclusion criteria

2.4.1

We will include patients who are eligible according to the following criteria:

1.Individuals aged between 20 and 70 years.2.Individuals who voluntarily sign the informed consent form for the clinical study, or those who are incapable of providing voluntary agreement but whose legal representatives sign the informed consent form.3.Individuals who are willing to cooperate and comply with regulations during the study period.4.Individuals who consent for blood collection for the purpose of this study.

For the study participants who meet the aforementioned criteria, the selection criteria for each group are as follows:

1.Ankle–brachial index (ABI) <0.9 or triglycerides ≥150 mg/dL and high-density lipoprotein cholesterol <40 mg/dL in men and <50 mg/dL in women2.Blood stasis score (≥9 points out of 32 total points)Group I (circulatory disturbance I): Meets both aforementioned criteria (1 and 2).Group II (circulatory disturbance II): Meets one of the aforementioned criteria (1 but not 2).Group III (normal): Does not meet either criterion from the aforementioned criteria.

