#### Secondary outcome

2.7.2

1.ABI is an indicator used to evaluate the degree of lower extremity artery stenosis or occlusion.^[20]^ The lower value between the left and the right measurements will be recorded.2.The brachial-ankle pulse wave velocity, an indicator of the brachial-ankle pulse wave velocity, is used to evaluate the presence or absence of the atherosclerosis progress in the main limb arteries.^[21]^3.Total cholesterol, triglycerides, and high-density lipoprotein cholesterol values.4.Blood pressure, body mass index, and waist circumference measurements.

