### Statistical analysis

2.10

A basic analysis of the study results will compare the difference in evaluation indicators of groups I and II (with circulatory disturbances) with that of group III (without circulatory disturbances) at visit 1. All statistical analyses will be subjected to two-tailed tests, and the significance level will be set at 5%. A descriptive analysis of the evaluation items and blood indices for each group will be conducted to represent the categorical variables as n (%) and continuous variables as mean ± standard deviation. To compare the intergroup differences for the obtained outcome value for each item, categorical variables will be subjected to the chi-square test and Fisher exact test, whereas continuous variables will be analyzed using the *t* test and analysis of variance or nonparametric methods such as Mann-Whitney *U* test and Kruskal-Wallis test for those not meeting the normality criteria. Analysis of covariance will be performed when it is necessary to control underlying variables, such as demographic variables (sex, age, weight, and height). For data with a missing value, the last observation carried forward will be used through CRF inspection to replace the missing value.

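### The blood stasis score is a primary outcome and also the cut-off that forms Group I, so its planned comparison with Groups II and III is circular; ABI, triglycerides and HDL-C are biased the same way against Group III, though less surely

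*Protocol article*

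**What the plan says.** Section 2.4.1 sets two rules. Criterion 1 begins "Ankle–brachial index (ABI) <0.9 or triglycerides ≥150 mg/dL and high-density lipoprotein cholesterol <40 mg/dL in men" and continues with a separate HDL-C limit for women. Criterion 2 is "Blood stasis score (≥9 points out of 32 total points". The groups follow from these: "Group I (circulatory disturbance I): Meets both aforementioned criteria (1 and 2"; "Group II (circulatory disturbance II): Meets one of the aforementioned criteria (1 but not 2"; and Group III meets neither.

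Section 2.7.1 has two primary items. The first is four blood markers: "Resistin, serum amyloid P component, C-reactive protein, and D-dimer are the candidate indicators that seem effective in diagnosing blood stasis". The second is the score: "Blood stasis score: A blood stasis questionnaire used to assess the presence/absence of blood stasis and to evaluate the blood stasis score". Section 2.7.2 lists ABI and "Total cholesterol, triglycerides, and high-density lipoprotein cholesterol values" among the secondary outcomes.

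Section 2.10 compares Groups I and II with Group III at visit 1, using two-sided 5% tests. It names the methods "To compare the intergroup differences for the obtained outcome value for each item" and makes no exception for variables that formed the groups. Section 2.6 places the questionnaire, ABI and blood tests at visit 1, within a week of registration. The text does not say whether the analysed values are those used for classification or fresh ones.

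**The concern.** A test between groups is informative only if the grouping leaves the outcome free to differ or not. Here one primary outcome defines the boundary of Group I, and three secondary outcomes define the boundary between Groups I and II together and Group III. A small p value for the score would restate the eligibility rule.

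The study aims to design a diagnostic technique and assess its validity (section 2.1), and the Discussion speaks of how well the diagnostic index works. A built-in difference in a primary outcome could easily be read as support for the questionnaire or for the group concept, although the data could hardly have shown anything else.

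**Working it through.** The protocol reports no power or effect size for this comparison (section 2.9 disclaims a calculation), so there is no figure to reproduce. The check has three parts.

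**1. Bounds implied by section 2.4.1.** Criterion 1 is read as ABI below 0.9, or high triglycerides together with low HDL-C.

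| | Group I | Group II | Group III |
|---|---|---|---|
| Score | 9 or more | below 9 | below 9 |
| Criterion 1 | met | met | not met |

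The rule therefore forces a score difference for I vs II and I vs III, but not for II vs III. It pushes ABI, triglycerides and HDL-C apart for I or II vs III, but not for I vs II.

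**2. Classifying score equals analysed score.** Groups I and III are completely separated. The exact two-sided Mann-Whitney p is then 2 / C(n1+n2, n1):
- 3 per group: 2/20 = 0.10
- 4 per group: 2/70 = 0.029
- 5 per group: 2/252 = 0.008

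This needs no assumption about the score's distribution.

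**3. Score re-measured at visit 1.** The score was simulated with no link to criterion 1. None of these inputs is in the protocol: mean 7, 9 or 11; SD 4; reliability between classification and visit 1 of 1.0, 0.8 or 0.6; group sizes 33/33/34, 25/25/50 or 20/40/40; 600 runs per setting; t test or ANOVA at two-sided 5%. The table gives the percentage of runs rejecting, as a range over means and group splits.

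| Reliability | I vs III | II vs III | I+II vs III | Three-group ANOVA |
|---|---|---|---|---|
| 1.0 | 100 | 4–6 | 95–100 | 100 |
| 0.8 | 100 | 4–6 | 63–99 | 100 |
| 0.6 | 97–100 | 4–7 | 36–77 | 97–100 |

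II vs III stays at the nominal rate, as the bounds predict. The simulation error is at most √(0.25/600) = 2 percentage points.

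**Criterion 1 variables.** ABI, log triglycerides and HDL-C were simulated as independent normals, with groups of 33/33/34 and reliability 1.0 or 0.7. Three assumed ABI distributions gave different shares of cases entering through ABI. The table gives the percentage rejecting for pooled I+II vs III.

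| Share entering by ABI | ABI | Triglycerides | HDL-C |
|---|---|---|---|
| 6% | 7–9 | 99–100 | 98–100 |
| 19% | 31–43 | 95–100 | 90–100 |
| 55% | 93–100 | 57–85 | 47–78 |

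For I vs II, all three variables reject in 4–6% of runs. Because criterion 1 is either/or, the more people enter by one route, the weaker the forced difference in the other.

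**The case against.** A reader might infer that all these group differences will be significant whatever the truth. The documents do not support that. Score II vs III and the criterion 1 variables I vs II are not forced. ABI against Group III can sit near the nominal rate if few participants qualify through ABI. For the secondary outcomes the defect is bias towards a difference, not certain significance.

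A reader might also infer that the whole primary analysis is compromised. It is not. Resistin, serum amyloid P, CRP and D-dimer are outside the grouping rule, as are pulse wave velocity, total cholesterol, blood pressure, BMI and waist circumference.

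Three further points can be made for the plan:
- Visit 1 follows screening, so the score may be re-measured and complete separation would then fail. This stands, but it weakens the circularity without removing it.
- The study is exploratory, and nowhere does it say that a score difference will be used to validate the questionnaire, whose validity section 2.7.1 credits to earlier work. No diagnostic accuracy estimate is planned in section 2.10. This limits the harm to a likely misreading, but an exploratory label does not make a built-in p value informative.
- The simulated rates depend on chosen inputs. This also stands, which is why ranges are given. The bounds and the exact p value do not depend on them, provided that the classifying score is the one analysed.

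Nor is this a detail to be left to an analysis plan: the protocol itself fixes the grouping rule, the outcomes and the comparison.

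**Conclusion.** The point holds in this form. The score contrast of Group I with II or III, and with it the three-group test, is built in by the grouping rule, and its p value says nothing about diagnostic value. Without re-measurement, I and III are fully separated. With re-measurement at assumed reliability 0.6–0.8, I vs III rejects in about 97–100% of runs and pooled I+II vs III in about 36–99%, against a nominal 5%, with no true link between score and metabolic status. ABI, triglycerides and HDL-C are biased towards a difference between Group I or II and Group III. How strongly depends on the route by which participants enter, which the protocol does not give. Since a primary outcome is affected, the plan should be changed before analysis.

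**What to change.** - **Section 2.7.1:** keep resistin, serum amyloid P, CRP and D-dimer as the only primary outcomes, and list the score as a classification variable.
- **Section 2.10:** report the score (I vs II or III, pooled and three-group) and ABI, triglycerides and HDL-C (I or II vs III) descriptively without p values, because they define the groups. Confine tests to variables not used for grouping. State whether visit 1 values are new measurements.
- **If the score is to be analysed:** relate the continuous score to each of the four markers within Groups I and II. Everyone there meets criterion 1, and the score runs across the cut-off. A regression over all three groups adjusted for criterion 1 is less safe: no group has a score of 9 or more without criterion 1, so at high scores the adjustment would rest on extrapolation.

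The cost is a change of wording, with no extra data. There will be fewer p values, including the unforced ones for score II vs III and criterion 1 variables I vs II, and one primary item is reclassified. The marker analysis uses only Groups I and II (66 people if the 100 split 33/33/34, an assumed split) and speaks only to people who meet criterion 1.

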### Intervention

2.6

Since this is an observational study, the treatment to improve circulatory disturbance is not restricted during the study. For a given period, treatment with Korean medicine, other Korean medical treatment, and prescription medication other than Korean medicine should be recorded. For Korean medicine, the name of the medicine, medicine composition, and treatment duration should be recorded.

For participants enrolled in the study after screening, we will perform blood tests; ABI and brachial–ankle pulse wave velocity measurement; blood stasis diagnosis questionnaire assessment; blood pressure, body mass index, and waist circumference measurement; and concomitant drug and Korean medical treatment assessment at visit 1 within 7 days of registration.

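### The doctor who rates the blood stasis score is not masked to the ABI and lipid results, and the interview is not placed before them, so expectation could influence borderline scores and group assignment

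*Protocol article*

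**What the plan says.** Protocol article, section 2.7.1 (Primary outcome), names the score as the second primary item: "Blood stasis score: A blood stasis questionnaire used to assess the presence/absence of blood stasis and to evaluate the blood stasis score". It is obtained by interview: "a Korean medicine doctor will directly interview each patient and complete the blood stasis questionnaire". The same sentence gives one safeguard: "By referring to the standard operating procedure of each question".

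Section 2.4.1 (Inclusion criteria) uses the score again as grouping criterion 2: "Blood stasis score (≥9 points out of 32 total points". Criterion 1 is built from ABI, triglycerides and HDL cholesterol. Group I meets both criteria, Group II meets criterion 1 only, and Group III meets neither.

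Section 2.6 (Intervention) sets out the assessments for people already enrolled: "For participants enrolled in the study after screening, we will perform blood tests; ABI and brachial–ankle pulse wave velocity measurement; blood stasis diagnosis questionnaire assessment", to be done "at visit 1 within 7 days of registration". Section 2.8 (Data collection and management) provides for coded patient identity, double data entry and verification against source data.

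**The concern.** One doctor-rated number serves both as a primary outcome and as the sole divider between Groups I and II. The results that define criterion 1 are the ones the rater might know. If they are known, a person near 9 points could be rated up when ABI or lipids are abnormal, or down when they look normal.

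Three things are at stake:
- **The Group I versus II split.** It would partly reflect what the rater expected to find.
- **Entry to Group III.** Someone who does not meet criterion 1 but scores 9 or more fits none of the three groups. A lower rating would admit that person as normal.
- **The apparent link between the score and circulatory disturbance.** The study aims to evaluate a diagnostic technique for metabolic disease with blood stasis. A link partly produced by the rating process would count in favour of that technique, and no analysis can remove it once the data are collected.

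**Working it through.** **1. What the text fixes.**

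| Question | Protocol article | Finding |
|---|---|---|
| Who rates? | 2.7.1 | A Korean medicine doctor, by interview |
| What limits discretion? | 2.7.1 | A procedure for each question; nothing on hiding results |
| When? | 2.6 | After screening, at visit 1, listed after blood tests, ABI and baPWV |
| Is the rater masked to ABI, lipids, screening findings or group? | All sections | Not stated |
| Is the interview placed first? | 2.6, 2.7.1 | Not stated |
| Do data procedures mask the rater? | 2.8 | No; they protect confidentiality and accuracy of entry |

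Table 1 and Figure 1 are not shown, so it is unclear whether the score used for grouping comes from screening or from visit 1. The text masks the rater at neither.

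**2. Who can be moved.** The document gives no mean or SD for the score, and section 2.9 (Sample size calculation) states that no effect-size calculation was made. There is therefore no figure of the plan's own to reproduce. What follows is an illustration with assumed inputs.

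Let the score among people who meet criterion 1 be normal with mean m and standard deviation s, and let expectation add b points. The share moved from Group II to Group I is

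Φ((9 − m)/s) − Φ((9 − b − m)/s).

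For b = 1:

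| Mean m | SD 3 | SD 4 | SD 5 |
|---|---|---|---|
| 5 | 6.7% | 6.8% | 6.2% |
| 7 | 11.7% | 9.3% | 7.6% |
| 9 | 13.1% | 9.9% | 7.9% |
| 11 | 9.4% | 8.2% | 7.0% |
| 13 | 4.3% | 5.3% | 5.3% |

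The range is about 4% to 13%. The upper end needs a mean near the cut-off and a small SD. With b = 0.5, m = 9 and s = 4, the share is Φ(0) − Φ(−0.125) = 0.500 − 0.450, or about 5%. Treating the score as whole points, with the boundary at 8.5, gives about 7% to 13% for a 1-point shift over means 7 to 11.

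**3. What a shift does to the score's link with criterion 1.** Suppose there is no true difference in score between people who do and do not meet criterion 1, and the rater adds b points only in the former. With 100 people split 50:50 and s = 4, the standard error is 4 × √(1/50 + 1/50) = 0.80. A two-sided 5% test is then significant with probability Φ(1/0.80 − 1.96) + Φ(−1/0.80 − 1.96) = 0.24 for b = 1. Across SD 3 to 5 and splits of 50:50 or 67:33, the probability runs from about 16% to 39%.

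This shows the direction of the effect only. It describes the score before people are sorted at 9 points, so it is not the error rate of the planned comparison of Groups I and II with Group III.

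**The case against.** The strongest reply is that the point rests on silence in a condensed article. The full protocol (version 1.2), the schedule table, the flow chart, the questionnaire appendix and the per-question procedures are not shown, and any of them may fix the order of assessments or who sees results. Section 2.7.1 also reports high reliability and validity for the parent questionnaire. Both parts carry weight, and the procedure does narrow the room for expectation. But it is not said to hide results, and the article describes in some detail how and by whom the score is obtained. Run in the order that section 2.6 lists, visit 1 would let the rater know criterion 1 results.

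Some stronger readings are tempting and are not supported:

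- **That the interview follows the tests.** Section 2.6 is a list without a stated sequence, and visit 1 laboratory results may not be back at the interview.
- **That the rater has seen the results, or that the protocol predicts stasis and circulatory disturbance go together.** Neither is stated. The aim is exploratory, and Group II exists for disturbance without stasis.
- **That upward rating must dilute the Group I versus II biomarker contrast.** A uniform 1-point rise among people who meet criterion 1 keeps their ranking and acts like a cut-off of 8. It dilutes only if 9 is the better cut, which the document does not establish.
- **That expectation decides the primary outcome.** It can influence scores near 9. The item 1 biomarkers are laboratory values that no rater can change.

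It is also fair that moving people between Groups I and II changes nothing if the two are pooled against Group III, and that the score's relation to group is largely set by the group definitions.

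**Conclusion.** The point holds as a moderate design weakness that is cheap to close. A clinician-rated score is both a primary outcome item and the sole separator of Groups I and II, it bears on entry to Group III, and the text leaves the rater free to know the results behind criterion 1. The likely effect is a different working cut-off for people who do and do not meet that criterion, with an inflated link between score and circulatory disturbance. Biomarker values stay sound, but comparisons between groups inherit any misgrouping.

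The illustrative 4% to 13% depends wholly on an assumed normal score, mean, SD and 1-point shift, and smaller shifts give less. It says how many could move, not how many will.

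**What to change.** In sections 2.6 and 2.7.1, require the questionnaire to be completed and signed before ABI and baPWV are measured and before any laboratory result is available to the interviewing doctor. Apply this at whichever visit supplies the score used for grouping, and say which visit that is.

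Reordering one visit does not hide results already obtained at screening. If criterion 1 results exist by then, keep them from the interviewing doctor until the form is signed. Have an existing team member other than the interviewer assign the group from the signed form and the results. Recording who rated and at what time would let readers check that the order was kept.

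The cost is slight scheduling and record-handling effort. No extra test or participant is needed.

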#### Secondary outcome

2.7.2

1.ABI is an indicator used to evaluate the degree of lower extremity artery stenosis or occlusion.^[20]^ The lower value between the left and the right measurements will be recorded.2.The brachial-ankle pulse wave velocity, an indicator of the brachial-ankle pulse wave velocity, is used to evaluate the presence or absence of the atherosclerosis progress in the main limb arteries.^[21]^3.Total cholesterol, triglycerides, and high-density lipoprotein cholesterol values.4.Blood pressure, body mass index, and waist circumference measurements.

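### baPWV may read low in participants who enter Groups I and II through ABI <0.9, so its comparison with Group III may be biased toward no difference

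*Protocol article*

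**What the plan says.** **Grouping (Protocol article, 2.4.1).** The first group-defining criterion is an ankle–brachial "index (ABI) <0.9 or triglycerides ≥150 mg/dL and high-density lipoprotein cholesterol <40 mg/dL in men and <50 mg/dL in women". The second is a blood stasis score of at least 9. Group I meets both criteria and Group II meets the first only. For the comparator the article says: "Group III (normal): Does not meet either criterion from the aforementioned criteria".

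**Outcomes (2.7.2).** On ABI: "ABI is an indicator used to evaluate the degree of lower extremity artery stenosis or occlusion". The side rule follows: "The lower value between the left and the right measurements will be recorded". baPWV is listed next as a measure that "is used to evaluate the presence or absence of the atherosclerosis progress in the main limb arteries". No side rule is given for baPWV.

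**Analysis (2.10).** The basic analysis sets the evaluation indicators of Groups I and II against those of Group III at visit 1, with two-sided tests at 5%. The covariates named for an optional analysis of covariance are sex, age, weight and height. Nothing in the article restricts, separates or adjusts the baPWV comparison by ABI.

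**The concern.** baPWV is a velocity derived from the timing of the pulse between arm and ankle. If an artery on that path is narrowed or blocked, the ankle wave can be damped and delayed. The derived velocity then falls for a reason unrelated to wall stiffness.

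The article itself reads ABI as a measure of narrowing or blockage in the leg, and it uses ABI below 0.9 to place people in Groups I and II. Any error of this kind therefore falls on the case side only. It is a systematic shift, which a larger sample would not average out.

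The study aims to judge diagnostic indices. If the most obstructed limbs contribute low readings, baPWV could be discounted as an index of circulatory disturbance for a measurement reason.

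**Working it through.** The article gives no baPWV mean, standard deviation, expected difference, group sizes or expected number with low ABI. Its total of 100 is stated not to rest on an effect size. There is thus no figure to reproduce, and what follows is a sensitivity check.

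**Step 1: where low ABI can occur.** Criterion 1 is read as ABI <0.9, or else raised triglycerides together with low HDL cholesterol.
- Group I requires criterion 1, so low ABI is possible.
- Group II requires criterion 1, so low ABI is possible.
- Group III fails criterion 1, so low ABI is not possible.

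**Step 2: effect in cm/s.** Let D be the true difference (Groups I and II minus Group III), q the share of Groups I and II with ABI <0.9, and e the downward reading error in those participants.

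Observed difference = D − q × e.

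Assumed, not from the article: D = 150 cm/s; e = 200 or 300 cm/s.

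| q | e = 200 | e = 300 |
|---|---|---|
| 10% | 150 − 20 = 130 | 150 − 30 = 120 |
| 20% | 150 − 40 = 110 | 150 − 60 = 90 |
| 40% | 150 − 80 = 70 | 150 − 120 = 30 |

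The sign changes only when q > D/e, that is above 150/200 = 75% or above 150/300 = 50%.

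**Step 3: effect on power, in SD units.** Assumed: true difference 0.5 SD, error 1 SD in low-ABI participants, 100 participants split 67/33 between Groups I and II together and Group III, two-sided 5%. The observed difference is 0.5 − q × 1.

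| q | Observed difference (SD) | Power |
|---|---|---|
| 0% | 0.50 | 65% |
| 2% | 0.48 | 62% |
| 5% | 0.45 | 56% |
| 10% | 0.40 | 47% |
| 25% | 0.25 | 22% |
| 50% | 0.00 | no difference left |

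With a 50/50 split the pattern is the same: 71% with no error, 61% at q = 5%, 52% at 10% and 24% at 25%. In SD units, reversal needs an error above 0.5/q: 10 SD at q = 5%, 5 SD at 10%, 2 SD at 25% and 1 SD at 50%.

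**Step 4: can this be repaired after data collection?** If only the lower ABI is kept, a participant with at least one leg below 0.9 can be identified. Which leg is affected, and whether both are, cannot. Whole participants could still be left out later, but the unaffected side could not be used.

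**The case against.** **The premise is not in the article.** No section says that baPWV reads low when ABI is below 0.9. This stands as a limit on certainty: the point is conditional. It rests on how an arm-to-ankle velocity is obtained, combined with the article's own description of ABI. It does not rest on a remembered figure.

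**The affected share may be very small.** ABI is one side of an alternative whose other side is lipids. The study concerns metabolic disease and recruits adults aged 20 to 70 partly through posters and advertisements. This stands. At q = 5% an assumed 0.50 SD difference becomes 0.45 SD.

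**A reader might infer that the comparison is certainly biased, or that it will point the wrong way.** The documents do not support either. The share is unknown, every scenario in the cm/s table keeps a positive difference, and on those figures reversal needs more than 50% to 75% of Groups I and II to have low ABI.

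**Validity rules for a device reading may sit in the full protocol or analysis plan.** That is possible. However, the article does fix a recording rule that keeps only the lower ABI, and the choice to keep both sides has to be made before data are collected.

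**Restricting to limbs with ABI of at least 0.9 has its own bias.** It removes the most diseased limbs, and some participants, from the case groups only. This stands, and it is why the restricted result should not replace the other.

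**Conclusion.** The point holds as a conditional one. The baPWV comparison may be biased toward no difference, because obstructed limbs can occur in Groups I and II but not in Group III and no handling of them is stated.

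The size cannot be fixed from the article. It is small if most participants enter by the lipid route. It becomes material if a sizeable minority enter by ABI: under the assumptions above, a quarter of cases with low ABI halves a 0.5 SD difference and cuts power from 65% to 22%. Reversal would occur only if low-ABI participants predominated or the error were very large.

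The conclusion rests on three assumptions: that obstruction lowers the derived velocity, that criterion 1 is read as in Step 1, and that at least some participants enter by ABI. One secondary outcome of an exploratory study is affected; the primary outcomes are not.

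**What to change.** 1. In the CRF, record left and right ABI and left and right baPWV, not only the lower ABI.
2. In 2.7.2 and 2.10, base the baPWV comparison on limbs with ABI of at least 0.9. Use the unaffected side if one leg is below 0.9, and leave out participants with both legs below 0.9.
3. Report the all-participant result alongside, with the number affected in each group.

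**Cost.** A sentence or two of text and the retention of each side's readings. The downside is that some case participants leave this one comparison and the remaining case mix shifts toward lipid-route entrants. At the assumed 67 participants in Groups I and II, 10% with low ABI would be about 7 people (0.10 × 67 = 6.7) and 25% about 17 (0.25 × 67 = 16.75). Only those with both legs affected would be lost. Because of that shift, both results should be shown, so that a reader can see how far the conclusion depends on the low-ABI limbs.
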